**Figure 2 F2:**
[figure not shown]
**Triangular region for study arms**. Showing the boundaries for analyzing the sequential trial using the Triangular test with the following parameters (p_0 _= 0.75, p_a _= 0.9, α = 0.05, β = 0.05, and n = 10). The vertical line at *n *= 30 indicates that, for the PK component of the trial, a minimum of 30 patients per arm will be recruited, unless the lower boundary has been crossed before then.

Each analysis consists of calculating the quantities *V *(proportional to current sample size) and Z (number of observed minus expected treatment successes) and plotting them on Figure 2. Hence, for each arm, a line from the origin is plotted over time. Recruitment in an arm will be stopped when this line crosses either boundary of the triangular region. Crossing the lower or upper boundary means concluding inadequacy or adequacy, respectively. Since the three arms will be assessed separately, it is possible that one of them may be stopped prior to others.

The above procedure is subject to a constraint imposed for the PK component of the trial, which requires at least 30 patients in arms 2 and 3, subject to efficacy not being inadequate. Therefore, if the upper boundary is crossed at *n *= 15 (indicating adequate efficacy) that arm will be continued regardless until *n *= 30. However, if the lower boundary is crossed (indicating inadequate efficacy) at *n *= 15, then it will be stopped.

Crossing a boundary of the region implies that the percentage of patients cured is either greater than 90% (if the upper boundary is crossed) or no more than 75% (if the lower boundary is crossed). The maximum likelihood estimate of the efficacy, i.e. the number cured divided by the number of patients, is a biased estimator due to the sequential nature of the trial. To take this into account, the analysis will follow Bellissant et al [11]. First, the sample quantity *C* *will be calculated as , where *V* *is the terminal value of *V *from the data sample, and the *θ*_*a *_parameter is the log-odds ratio *θ *= log_e_(*p*(1- *p*_0_)/*p*_0_(1- *p*)) for *p *= *p*_*a*_. Then, the tables in Whitehead's Appendix A [12] will be used to obtain the significance level of the test, and point and interval estimates of *p*. The latter are provided in terms of factors by which to multiply *θ*_*a*_. Finally, these three values of *θ *(i.e. point estimate and upper and lower confidence limits) will be transformed to corresponding sample values of *p *by *p *= (*p*_0_*e*^*θ*^)/(1+ *p*_0_(*e*^*θ*^-1)). Analysis will be done using STATA [14].

#### Analysis of secondary endpoint: cure at day 210

The sequential analysis described above relates only to efficacy on day 28, not day 210. However, because the latter is likely to be highly correlated with the former, ignoring the sequential design in the latter analysis could give inconsistent results. For example, if the status of all patients is the same at day 210 as at day 28, then using different methods for analysis would give different efficacy estimates from the same data. This is because the day 28 estimate takes into account the sequential design which, in general, would differ from conventional analysis done on the same data at day 210.

Therefore, the day 210 efficacy will be estimated by considering it in terms of events over two consecutive time periods: up to day 28, and from day 28 to day 210. More specifically, the day 210 efficacy (i.e. percentage cured or *p*_210_) will be considered as the sum of two probabilities, as follows:

i) probability of being cured at day 28 and remaining cured at day 210.

ii) probability of not being cured at day 28 but becoming cured at day 210.

Each of these probabilities is the product of two terms and enables a point estimate of *p*_210_:

where:

*r *is the percentage of those people cured at day 28 who remain cured at day 210.

*s *is the percentage of those people not cured at day 28 who become cured at day 210.

The confidence interval will be estimated via the sampling variance of *p*_210_. Using the 'delta method' [15], this can be estimated as a function of the sampling variances of *p*_28_, *r *and *s*; these three quantities being statistically independent. The sampling variance of *p*_28 _will be estimated as the square of its standard error, which in turn will be estimated as the width of its 95% confidence interval divided by 2 × 1.96, using a normal approximation. The sampling variances of *r *and *s *will be estimated by considering them as standard binomial proportions.

The above procedure ensures that, for example, if no patients change cure status between day 28 and day 210 then the point estimates of *p*_28 _and *p*_210 _will be equal (because *r *= 1 and *s *= 0). The confidence intervals will, however, generally be unequal. This is because treating the progress between day 28 and day 210 as a separate variable implies additional sampling variation. For example, *r *has sampling variation even when equal to 1. Moreover, sampling variation is considered on the probability scale, not the log-odds scale as for *p*_28_. This also means that the calculated confidence interval could exceed the interval 0-1. In this case, it will be truncated at the limits of that interval.

When the analysis results in an arm being stopped, the final cure rate (day 210) will also be evaluated (when all those patients have reached that time point). If the point estimate of the day 210 cure rate is found to be <90%, then the arm (arm 1 & 2) will not be considered for further study (e.g phase 3).

Within each arm, the percentage cured at each time point will be presented by site. Chi-squared or Fisher's exact tests will be used to test for differences between sites in terms of primary and secondary efficacy endpoints at the 5% level of significance.

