**Methods/Design:**

A phase II randomized, parallel arm, open-labelled trial is being conducted to assess the efficacy of each of the three regimens: liposomal amphotericin B with SSG, Liposomal amphotericin B with miltefosine and miltefosine alone. The primary endpoint is cure at day 28 with secondary endpoint at day 210 (6 months). Initial cure is a single composite measure based on parasitologic evaluation (bone marrow, spleen or lymph node aspirate) and clinical assessment. Repeated interim analyses have been planned after recruitment of 15 patients in each arm with a maximum sample size of 63 for each. These will follow group-sequential methods (the triangular test) to identify when a regimen is inadequate (<75% efficacy) or adequate (>90% efficacy). We describe a method to ensure consistency of the sequential analysis of day 28 cure with the non-sequential analysis of day 210 cure.

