### Analysis and sample size

#### Analysis of primary endpoint: cure at day 28

The study is designed and will be analyzed according to group-sequential methods, specifically the triangular test [10-12]. Following the trials main objectives, the aim of the analysis is to efficiently identify a regimen that is a) inadequate, so its development can be discontinued, or b) adequate, so its development can proceed. In these terms, the highest efficacy (i.e. percentage of patients cured as per primary outcome) considered inadequate is set in this trial to be 75% (denoted p_0_), and the lowest efficacy considered adequate as 90% (denoted p_a_). The null and alternative hypotheses are *H*_0_: *p *≤ *p*_0 _and *H*_1_: *p *>*p*_a _respectively.

The triangular stopping boundary, as shown in Figure 2, was defined following Ranque et al [10]. With both type I and type II error rates set at 5% (power 95%), and sequential analysis being done after every 15 patients per arm, the maximum sample size required is 189 (63 per arm). The actual sample size may be less than this, depending on when the actual percentage of patients cured leads to a boundary being crossed. The boundaries were calculated using custom-written functions in the R software [13], having checked that they could reproduce the example in Ranque et al [10].

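### The Figure 2 caption lists n = 10 among the boundary parameters, which does not fit the text's looks every 15 patients and maximum of 63 per arm; and 63 is not a scheduled look

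*Protocol article*

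**What the plan says.** The protocol article, under Analysis of primary endpoint, gives the design as "sequential analysis being done after every 15 patients per arm, the maximum sample size required is 189 (63 per arm"). The abstract agrees: looks come "after recruitment of 15 patients in each arm with a maximum sample size of 63 for each". The paragraphs after the Figure 2 caption discuss a boundary crossing at n = 15, and Dissemination of Results has the first DSMB report after 15 patients per arm.

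The caption of Figure 2 lists the parameters of the plotted boundaries as p0 = 0.75, pa = 0.9, "α = 0.05, β = 0.05, and n = 10". It does not define n. The text below it makes the figure the working tool: V and Z are computed at each analysis and plotted on Figure 2, and an arm closes to recruitment once its path leaves the triangle. Nothing in the article reconciles 10 with 15, and nothing says how an analysis at 63 would be made.

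**The concern.** Apart from the hypotheses and error rates, the only other design input of a group-sequential triangular test is the number of patients between looks. The caption lists the hypotheses and error rates, so the natural reading of its last item is that group size. Group size matters because the boundaries are pulled inwards to allow for looking only at intervals; a smaller group gives a smaller correction and a wider triangle. If 10 and 15 both appear as the group size, the document describes two stopping charts.

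At stake are the verdict on an arm in a borderline case and the stated maximum size. There is a second, smaller point. Looks every 15 patients fall at 15, 30, 45 and 60, so 63 does not lie on the schedule.

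**Working it through.** **Inputs from the document.** p0 = 0.75, pa = 0.90, type I and type II error both 0.05 (taken as one-sided, since the hypotheses are directional), looks every 15, maximum 63. V is described only as "proportional to current sample size) and Z (number of observed minus expected treatment successes".

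**Inputs assumed.** Z = S − 0.75n, where S is the number cured; V = n·p0(1 − p0) = 0.1875n; and the usual discrete-look correction 0.583·√(V per group). The article states neither the form of V nor the correction.

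**Formulas.** With g patients per look:

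- θ = ln[0.90 × 0.25 / (0.75 × 0.10)] = ln 3 = 1.0986
- a = (2/θ)·ln[1/(2 × 0.05)] = 4.192; c = θ/4 = 0.2747
- a′ = a − 0.583·√(0.1875g)
- Upper boundary Z = a′ + cV; lower boundary Z = −a′ + 3cV
- The boundaries meet at V = a′/c, so the maximum n = a′/(0.1875c)

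**Reproducing the plan's figure.** For g = 15, a′ = 4.192 − 0.978 = 3.214 and the maximum is 62.4, rounded up to 63 per arm (189 in total). This is the stated value. Without the correction the maximum would be 81.4; with α = 0.025 and the correction it would be 86.9. Neither variant fits, so the assumed forms are supported.

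**The caption's value.** For g = 10, a′ = 4.192 − 0.798 = 3.394 and the maximum is 65.9, rounded up to 66 per arm (198 in total).

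**Cut-offs in numbers cured, on looks of 15** (boundaries converted by adding 0.75n):

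| n | g = 15: stop low / stop high | g = 10: stop low / stop high |
|---|---|---|
| 15 | ≤10 / none | ≤10 / none |
| 30 | ≤23 / ≥28 | ≤23 / ≥28 |
| 45 | ≤37 / ≥40 | ≤37 / ≥40 |
| 60 | ≤51 / ≥52 | ≤50 / ≥52 |

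Only 51 of 60 is treated differently: inadequate under g = 15, continue under g = 10.

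**How often that outcome arises.** An exact binomial recursion carries forward, look by look, only the paths that have not crossed. The probability of arriving at 51/60 is 1.2% at a true cure rate of 0.75, 6.1% at 0.82, 7.4% at 0.85 and 3.5% at 0.90.

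**Can 63 be reached?** At n = 60, V = 11.25. With g = 15 the lower boundary is Z = −3.214 + 9.270 = 6.055 (difference in the last digit is rounding) and the upper is 3.214 + 3.090 = 6.304. In cures this is 51.06 to 51.30, an interval that holds no whole number. Every possible count at n = 60 therefore gives a decision, and the probability of continuing is exactly 0. With g = 10 the interval is 50.88 to 51.48, which holds 51, but neither 63 nor 66 is then a look on the 15-patient schedule.

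**The case against.** The strongest objection is that the fault may lie only in the caption. The figure is not shown, and the caption does not define n; it uses the same letter for the number of patients in an arm when it explains the line at n = 30. The analysis section presents the boundary in Figure 2 as the one with looks every 15, the interval of 15 appears in four places, and 63 is reproduced from 15 and not from 10. A slip in the caption over a correctly drawn figure is at least as plausible as a misdrawn figure. This stands. A reader might infer that Figure 2 is plotted for looks every 10 and that decisions will be taken on the wrong boundaries; the document does not show that.

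Next, the disagreement is narrow. On the planned looks it touches one outcome, and its probability is largest at cure rates between the two design values. This also stands.

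A reader might go on to infer that an arm could run to 75, beyond the stated cap. That needs a figure drawn for 10, exactly 51/60, and disregard of the stated maximum. The article plans none of this.

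A reader might also blame the caption for power below 95%. The calculation does not support that: by n = 60 the probability of declaring adequacy at a true rate of 0.90 is 86.1% under either triangle. The shortfall is a separate issue.

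Finally, 63 is the tip of the triangle, and the article says that the actual number may be smaller. As an upper limit it is safe, and it alters no decision. What remains is that it overstates the attainable decision sample by 3 per arm, 9 in total, and suggests an analysis that the schedule does not contain.

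**Conclusion.** The inconsistency is real but limited. If n in the caption is the group size, the caption (maximum 66) and the text (maximum 63) cannot describe the same triangle. One of them needs correcting, and the document does not show whether the plotted boundaries are affected or only the caption.

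If the plotted boundaries are affected, the consequence on looks of 15 is confined to 51/60, with the probabilities given above. If they are not, only a label is wrong. Separately, under the group-15 boundaries the largest sample at which a decision is taken is 60 per arm. Recruitment while day-28 results are awaited could take enrolment above 60, but would not change the decision at 60.

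These results rest on V = 0.1875n, the 0.583 correction and a one-sided α of 0.05. The first two are not stated in the article and are supported by reproducing 63.

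**What to change.** - Check in the boundary code which group size Figure 2 was drawn with. If it was 15, correct the caption and define n there; if it was 10, redraw the figure for 15.
- State the maximum decision sample as 60 per arm (180 in total). Alternatively, name n = 63 as a final look and give its cut-off. Under the assumptions used here that would be ≤53 inadequate and ≥54 adequate; since the group-15 boundaries leave no arm undecided at 60, such a look would have to replace the one at 60.
- As an optional aid, print the integer cut-offs for g = 15 from the table beside the figure, so that no decision depends on reading a plot.

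The cost is a caption, at most one redrawn figure, and one line of text. The look schedule of 15 does not change unless 63 is chosen as the final look.

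### Crossing a boundary is said to imply cure above 90% or at most 75%; the triangular test shows only that cure exceeds 75% or is below 90%

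*Protocol article*

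**What the plan says.** All of this is in the protocol article, mainly under Analysis and sample size, subsection Analysis of primary endpoint: cure at day 28.

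- **Design points.** The highest efficacy "considered inadequate is set in this trial to be 75"% (p_0), and "the lowest efficacy considered adequate as 90"% (p_a). The null hypothesis is p ≤ p_0 and the alternative is p > p_a.
- **Error rates and looks.** "With both type I and type II error rates set at 5% (power 95"%), with "sequential analysis being done after every 15 patients per arm". On size the article states that "the maximum sample size required is 189 (63 per arm").
- **Decision labels.** After Figure 2: "Crossing the lower or upper boundary means concluding inadequacy or adequacy, respectively".
- **Interpretation.** The text then goes further: "Crossing a boundary of the region implies that the percentage of patients cured is either greater than 90% (if the upper boundary is crossed"). A lower crossing is likewise taken to mean a cure rate of 75% or below.
- **Abstract.** The sequential method is described as a way "to identify when a regimen is inadequate (<75% efficacy) or adequate (>90% efficacy").

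The sentences after the interpretation rule say that the raw proportion is biased by the sequential design. They plan a significance level, an adjusted point estimate and an adjusted interval. The day 210 subsection adds that arms 1 and 2 are not taken further if the day 210 point estimate is below 90%.

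**The concern.** A sequential test with two design points controls the chance of a wrong decision at those two points. It does not sort the true rate into one of two ranges. The interpretation sentence turns a decision label into a claim about the size of the effect, and the claim is too high after an upper crossing and too low after a lower one. The hypotheses have the same gap, since a true rate of 80% or 85% is covered by neither.

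The sentence is the stated reading of the primary endpoint. The triangular analysis goes to the DSMB and informs whether development of a regimen proceeds or is discontinued. The miltefosine monotherapy arm is also meant to support registration. Read literally, the rule would let a regimen curing 85% be described as curing more than 90%, or as curing no more than 75%, depending on chance.

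**Working it through.** **1. Logic, which needs no reconstruction.** Every run ends at one of two boundaries. The attached statements are p > 90% and p ≤ 75%. If 75% < p < 90%, neither is true, so the conclusion is false whichever boundary is crossed. With the supported statements (upper: p > 75%; lower: p < 90%), both are true throughout that range.

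**2. Reproducing the stated maximum.** Inputs from the article: p_0 = 0.75, p_a = 0.90, α = β = 0.05, groups of 15. Z is observed minus expected successes, so Z = S − 0.75n. Assumptions: V = n·p_0(1 − p_0) = 0.1875n (the article says only that V is proportional to n), and the usual 0.583 correction for discrete looks.

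- θ_a = ln[0.90 × 0.25 / (0.75 × 0.10)] = ln 3 = 1.0986
- a = (2/θ_a)·ln[1/(2α)] = 4.192; c = θ_a/4 = 0.2747
- Information per group: 15 × 0.1875 = 2.8125; a′ = 4.192 − 0.583·√2.8125 = 3.214
- Upper boundary Z = a′ + cV; lower boundary Z = −a′ + 3cV. They meet at V = a′/c = 11.70, so n = 11.70/0.1875 = 62.4, rounded up to 63.

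This matches the stated 63. Groups of 10, as in the Figure 2 caption, give 65.9, which does not.

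**3. Boundaries in numbers cured (groups of 15).**

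| n | lower crossed at | upper crossed at |
|---|---|---|
| 15 | ≤ 10 | not reachable |
| 30 | ≤ 23 | ≥ 28 |
| 45 | ≤ 37 | ≥ 40 |
| 60 | ≤ 51 | ≥ 52 |

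An upper crossing can occur at 40/45 (88.9%) or 52/60 (86.7%), and a lower crossing at 37/45 (82.2%). So the sentence fails even if the percentage cured means the observed rate. Exact 95% binomial intervals that ignore the sequential design are 75.9 to 96.3% for 40/45 and 75.4 to 94.1% for 52/60. Neither comes near to showing a rate above 90%.

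**4. Probability of each conclusion by true rate.** Exact binomial recursion, looks at 15, 30, 45, 60 and 63:

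| True rate | upper (called > 90%) | lower (called ≤ 75%) |
|---|---|---|
| 75% | 3.2% | 96.8% |
| 80% | 15.3% | 84.7% |
| 85% | 47.1% | 52.9% |
| 87.5% | 68.1% | 31.9% |
| 90% | 86.1% | 13.9% |

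**5. Sensitivity to group size.** With groups of 10, an upper crossing at a true 85% has probability 52% if the maximum is that design's own 66, and 54% if it is capped at 63. An upper crossing is still possible at 52/60.

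**The case against.** The strongest defence is that this is an ordinary indifference-zone design. The two rates are defined as the highest considered inadequate and the lowest considered adequate, and either decision is tolerable between them. On that view the labels adequate and inadequate are legitimate, the abstract is shorthand, and only one sentence overreaches. The plan also commits to adjusted estimates and intervals, which would show the real uncertainty, and the day 210 rule checks an over-optimistic upper crossing.

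Much of this stands. The labels are sound as decisions, and the design is not at fault. It does not rescue the interpretation sentence, which asserts a numerical efficacy. The day 210 rule does not cover arm 3, rests on a point estimate, and does nothing for an arm wrongly described as at most 75%.

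A reader might infer more than the document supports:

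- *That arms will be reported as above 90% or at most 75%.* The article does not say so; it plans adjusted estimates.
- *That the counts in the working are the plan's own boundaries.* They are not printed, and Figure 2 is not shown. The text provides for an upper crossing at n = 15, which the reconstruction cannot reach (15/15 gives Z = 3.75 against 3.99).
- *That 51/60 and 52/60 receive opposite conclusions.* This holds only with groups of 15. With groups of 10 the lower limit at 60 is 50, so 51/60 does not stop low.
- *That a lower crossing rejects p ≥ 90% at 5%.* On the reconstruction its probability at 90% is 13.9% (groups of 15) or 10 to 11% (groups of 10), so corrected wording should not attach that figure.

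**Conclusion.** The point holds as an error of interpretation and of how the alternative is written. An upper crossing supports p > 75%, and a lower crossing supports p < 90%. For true rates strictly between 75% and 90%, both of the article's statements are false; that follows from logic alone.

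The size is illustrative. At a true 85% the claim of more than 90% would be made in about 47% of runs with looks every 15 patients, or 52 to 54% with looks every 10, and the claim of at most 75% in the remainder. These figures rest on V = 0.1875n and the 0.583 correction.

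The severity is moderate. Boundaries, sample size and estimators do not change, adjusted estimates are already planned, and arms 1 and 2 have partial protection at day 210. Arm 3 does not.

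**What to change.** Replace the interpretation sentence with wording such as:

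> Crossing the upper boundary rejects p ≤ 75% and leads to the decision adequate. Crossing the lower boundary is evidence against p ≥ 90% and leads to the decision inadequate. Neither crossing shows that efficacy exceeds 90% or is at most 75%; any numerical statement of efficacy rests on the bias-adjusted estimate and its confidence interval.

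Write the alternative hypothesis as p > p_0, with power evaluated at p = 0.90, so that the 75 to 90% range is no longer outside both hypotheses. Align the abstract, so that its two cut-offs read as design points and not as findings.

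The cost is wording only. The price is a less favourable claim after an upper crossing.

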### Schedule of Assessments and Expected Side Effects

Assessments are timed at days 0, 3, 7, 14, 21, 28, 60 and 210 (Table 1) and include clinical, parasitology, haematology, biochemistry and pharmacokinetic assessments (table 1). Baseline assessments include anthropometric, clinical and lab evaluations. Day 60 and 210 assessments require some flexibility on dates due to patient travel, visit windows for each is as follows- day 60 (+/- 10 days) and day 210 (+/- 21 days).

**Table 1 T1:** Schedule of events

SCHEDULE OF EVENTS																									
**Protocol Activities and Forms to Be Completed**	**Screening (day)**				**Treatment (day)**																			**At Follow-up after day 30**^1^	
			
			**-2**	**-3**				**4**	**5**	**6**	**7**									**21**					**Day 60 Day 210**

Consent form &																									

											X							X		X		X		X	X

	X																					X			X ^2^

rK39 dipstick	X																								

ECG	X										X							X							

	X										X							X						X	

	X						X				X							X						X	

	X										X							X				X			

	X										X							X				X		X	X

																									

						X	X	X	X	X	X	X	X	X	X										

					X																				

						X	X	X	X	X	X	X	X	X	X										

					X	X	X	X	X	X	X	X	X	X	X	X	X	X		X		X			

**PK study for Miltefosine - Arm 2 - A*dults5***						X^6^		X			X				X									X	X

**PK study for Miltefosine - Arm 2 - *Children5***						X^6^					X				X									X	X

**PK study for Miltefosine - Arm 3 - A*dults5***					X^6^		X				X							X		X		X		X	X

**PK study for Miltefosine - Arm 3 - *Children5***					X^6^						X							X				X		X	X

Volume of blood (ml) taken from Group 2 - children	7.5					2.5	2.5				10.5				0.5			10				7.5		7.5	7.5

Volume of blood (ml) taken from Group 3 - children	7.5				2.5		2.5				10.5							10.5				8		7.5	7.5

^1 ^Patients assessment between day 60 and 210 in the event of any medical problems. Blood count, biochemistry, liver function tests parasitology and PK analysis will be done in the event of such a visit. At the day 210 visit, flexibility (of +/- 30 days) will be allowed for timing due to practical difficulties patients may face to meet exact timing of visits.

^2 ^Parasitology will be done in the follow up period after day 28 if clinically indicated (i.e. if reappearance of symptoms and signs of VL).

^3 ^2.5 ml of EDTA blood for Complete blood count; and only 0.2 ml EDTA blood used for PCR

^4 ^7.5 ml blood for urea, creatinine, liver function test.

^5 ^The PK study will be done on the specified days with 2.5 ml of EDTA blood taken before/after and 0.5 ml during treatment (the possible use of dried blood spots is currently under investigation).

^6 ^On first day of Miltefosine treatment, blood samples will be drawn 3 times: just prior to first dose, 4 & 8 hours post-dose to assess the absorption-phase of miltefosine (total volume needed 2.5 ml).

Volumes of blood required for children are shown in bottom two rows. In total, 41.5 ml are required in the first 1 month during admission in group 3 and 41 ml for group 2.

Clinical assessments will include pulse, blood pressure, temperature, weight, height (done only at baseline), spleen size, liver size.

